#### BI/RT+

Participants in the BI/RT+ condition attended 2–6 (20–40 min each) audio-taped sessions that were intended to approximate the provision of severity-appropriate expanded brief intervention. The first session occurred at the primary care site on the same day that the participant enrolled into the study, and subsequent sessions occurred at the primary care site within the following 12 weeks. Similar to the BI/RT condition, the BHC employed MI techniques to explore the patient’s perspective on their substance use. However, the BHC modeled their motivational techniques after the Motivational Enhancement Therapy (MET) approach employed in Project Match [26]. This approach spreads brief intervention over sessions, allowing the BHC more time to negotiate a change plan with the patient. In addition, the BHC had numerous tools, described in more detail below, that they could employ over these multiple brief intervention sessions to assist patients in achieving their goals. Just as in the BI/RT condition, exploring a referral to treatment was a standard component of BI/RT+. Patients with scores in the “mild” and “moderate” severity range received MET geared towards helping them set a reduction or abstinence goal and a strategy for following up on this goal. “Mild” and “moderate” severity patients were generally not referred out to community counseling resources, rather they were offered up to six sessions of brief intervention that incorporated cognitive-behavioral strategies or 12-Step facilitation strategies to assist them in pursuing their reduction or abstinence goals. Patients who screened in the “severe” problem range were typically referred out to specialty care. However, the BHC was instructed to utilize repeated sessions of brief intervention to resolve treatment entry barriers with patients. Furthermore, after referred patients connected with specialty care, the BHC could offer 1–2 interventions to process patient reaction to the treatment experience and augment motivation to remain in specialty care.

BHCs provided ongoing telephone monitoring to patients assigned to BI/RT+ using RecoveryTrack^®^. RecoveryTrack^®^ is a patient interview conducted by the BHC over the phone and includes a web-based monitoring instrument that allows a treatment system to tailor a selection of outcome items to follow throughout the course of substance abuse treatment. The BHCs used the information they collected on RecoveryTrack^®^ to monitor the BI/RT+ patients and to determine if they needed any additional information, services, or treatment referrals.

### Intervention materials

Our team developed a flexible brief treatment toolkit that a behavioral health clinician can use to deliver standard SBIRT, various MET and CBT interventions, as well as basic 12-Step Facilitation and SUD treatment psychoeducation. It comprises a menu of 35 loosely linked interventions adapted for primary care; each intervention can be covered in 5–15 min, and includes patient takeaways so that concepts can be revisited out of the office. Much of the content of the “toolkit” has been presented neutrally around the concept of breaking habits, rather than focusing only on substance use, so the materials are useful for other purposes. The BHC introduces the toolkit cards during a counseling session, and encourages the patient to use the cards as educational materials and reference resources after leaving the session. Additionally, we designed a graphic novel as a supplemental component of the toolkit. The graphic novel introduces patients to two characters engaging in change related to substance use, and it provides patients with health information and activities to promote behavioral change.

### Patient follow-up procedures and outcome measures

Patients in both the BI/RT and BI/RT+ conditions were asked to complete follow-up assessments every 3 months following baseline for 1 year (i.e., at 3, 6, 9, and 12 months post-recruitment). Assessments took place in person, generally at the health center where the patient was recruited.

Table 2 provides a summary of each of the variables involved in the trial and indicates the relevant purpose of the variable, the instrument used to assess that variable, and the assessment points where the instrument was delivered.

**Table 2 Tab2:** Outcome variables and assessment points

Variable	Purpose	Instrument	Assessment points
Drug and alcohol problems	Screen, randomize	AUDIT, DAST-10	Screening
Intervention and treatment engagement	Hypothesis 1	NSMOS, patient charts	Baseline, 3-, 6-, 9-, 12-months
Drug use and severity	Hypothesis 2	ASI, urinalysis, MINI	Baseline, 3-, 6-, 9-, 12-months
Medical and psychosocial functioning and HIV risk	Hypothesis 3	ASI, HIV-RA, chronic conditions Questionnaire, healthy days	Baseline, 3-, 6-, 9-, 12-months
Readiness to change and personal stress	Covariates	Personal rules, PSS-4	Baseline, 3-, 6-, 9-, 12-months
Patient satisfaction	Evaluation	Client satisfaction form	3-months

#### Outcome measures

Primary endpoints of substance use will be measured using an abbreviated version of the *Addiction Severity Index-6th Edition (ASI6)* [50, 51] and urinalyses. The ASI is a multi-dimensional interview used to measure problem severity of substance use, health, and social problems. We used an abbreviated version of the ASI6 that takes approximately 20 min to complete.

*Urinalysis* Urine analyses were conducted using an 8-panel screen that covers the most commonly abused illicit drugs, including marijuana, cocaine, amphetamine, methamphetamine, morphine/opiates, benzodiazepines, barbiturates, and PCP.

*Non*-*Study Medical and Other Services (NSMOS)* The NSMOS was specifically developed for this study and records the number of additional community and specialty care treatment services that patients received for medical, psychiatric, and drug and alcohol needs. The NSMOS also assesses whether the patient received these services in outpatient or acute care settings.

*Severity past year: MINI Plus 5.0.0* The MINI is a short, structured diagnostic interview for DSM-IV and ICD-10 psychiatric disorders [52, 53].

*Chronic Conditions Questionnaire* The Chronic Conditions Questionnaire assesses how well patients manage chronic diseases or conditions.

*Healthy Days Symptoms* The Healthy Days Symptoms measures the number of days over the past month that a patient was affected by symptoms such as pain and anxiety, as well as the number of healthy days.

*Perceived Stress Scale 4*-*Item Version (PSS-4)* The PSS is a global measure of the perception of stress, and has been shown to be correlated with quitting smoking and other measures of health behaviors [54].

*Personal Rulers* The Personal Rulers measure a patient’s perception of importance, readiness, and confidence in reducing or quitting their drug and/or alcohol use.

*HIV Risk Assessment (HIV-RA)* The HIV Risk Assessment provides a brief self-report measure of HIV testing history and sexual risk.

*Client Satisfaction* A Client Satisfaction Form was administered to participants at the 3-month follow-up to assess participant satisfaction and perceived usefulness of the interventions.

### Counselor fidelity measures

As described earlier, all counseling sessions in both conditions were audio recorded, and a random selection of tapes was reviewed by a clinical supervisor to monitor fidelity. We trained research assistants to code a randomly selected 20 % of recordings for intervention integrity using an SBIRT checklist and key BI/RT or BI/RT+ component items from the Yale Adherence and Competence Scale (YACS; [55]). The YACS is a scale for the assessment of clinician adherence to protocol and competence in delivering substance abuse treatment. The SBIRT checklist contained a list of all BI/RT and BI/RT+ activities. For 25 % of the selected recordings, a second research assistant independently completed the integrity instruments for reliability purposes.

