### Intervention procedures

All participants were screened for risky substance use prior to being invited to enroll in the study. Eligible participants consenting to the study were assigned to BI/RT or BI/RT+ via a block randomization procedure. Half of the patients identified with risky substance use received BI/RT and half received BI/RT+. Research assistants were responsible for assigning participants to conditions using a website programmed with the allocation sequence created by the study’s statistician. Participants, BHCs delivering the intervention, and research assistants were not blinded to group assignment.

In both conditions, all counseling sessions were digitally audio-recorded and securely stored in order to complete supervision and intervention integrity analyses. Throughout the trial, a clinical supervisor and expert in SBIRT reviewed 1 to 2 randomly selected sessions for each BHC each month and provided at least bi-weekly supervision with BHCs to (a) review the BI/RT or BI/RT+ content covered in meetings, (b) reinforce the BHCs’ adherence to the protocol, (c) discuss any protocol breaks that occurred in prior patient meetings, and (d) address any therapeutically relevant issues that might be occurring (e.g., new problems, ethical issues).

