A second limitation is the potential for condition contamination. In this study, each BHC provided both BI/RT and BI/RT+. The alternate method would be to assign independent BHCs to each condition. The primary advantage associated with nesting providers across interventions, such that each BHC provides both interventions, is that non-specific provider variables are equalized across conditions. The disadvantage associated with this approach is the increased likelihood of condition contamination or “bleeding,” given that providers are administering both interventions and may introduce methods of one intervention into the other. We have elected to nest BHCs across conditions because: (1) we can identify, specify, and measure “bleeding” more clearly than non-specific provider variables; (2) we can take actions to manage protocol violations; and (3) we can assess the influence of intervention integrity on our dependent measures more readily than we can assess the influence of non-specific provider factors.

A final limitation is that we did not conduct hair analysis and used only urinalysis. Hair testing would have allowed us to obtain a biological measure of substance use covering a longer period of time.

By conducting a large-scale randomized trial in real-world health centers, this study will answer important questions about the effectiveness of expanded SBIRT in primary care settings. Furthermore, our economic evaluation and process evaluation will provide additional context for health systems that are considering implementing brief treatment interventions.

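### Integrity recordings are coded and second-coded by research assistants, a group described as unblinded, so the contamination measure is open to rater expectation bias of unknown size and direction

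*Protocol article*

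**What the plan says.** Three parts of the protocol article bear on this.

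- **Intervention procedures.** Blinding is described in one unqualified sentence: "Participants, BHCs delivering the intervention, and research assistants were not blinded to group assignment". The same staff group handles allocation: "Research assistants were responsible for assigning participants to conditions using a website programmed with the allocation sequence".
- **Counselor fidelity measures.** The integrity data come from the same group: "We trained research assistants to code a randomly selected" fifth of the recordings, with an SBIRT checklist and "key BI/RT or BI/RT+ component items from the Yale Adherence and Competence Scale". The checklist is said to list the activities of both conditions. For 25% of the coded recordings a second research assistant completes the instruments independently, as a reliability check. Nothing is said about hiding the arm from either coder.
- **Discussion, limitation on contamination.** Each BHC delivers both arms, and the article concedes that this raises the chance of methods crossing between them. It gives three reasons for accepting this. The first is that "we can identify, specify, and measure" such bleeding more clearly than non-specific provider variables. The second is that protocol violations can be managed. The third is that the influence of intervention integrity on outcomes can be assessed.

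**The concern.** The first and third reasons need a credible measure of what was delivered in each session. The coding of recordings is the only quantitative integrity measure the article describes, and both its main coding and its reliability check are given to a group it calls unblinded. A coder who knows the arm may hear what that arm is supposed to contain, or may be over-alert to departures from it. Either way the recorded contamination rate moves away from the true one.

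This matters most if the trial finds little or no difference. The arms share BHCs, motivational interviewing, a same-day first session and exploration of referral. A reader will want to know whether BI/RT+ added nothing or whether BI/RT sessions had come to resemble it. A biased contamination measure would point the reader to the wrong explanation.

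**Working it through.** The article gives no figure for contamination or coder error, so there is nothing to reproduce. The check is a reading of the sections together, plus two small calculations.

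**Step 1. The chain in the text.**

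1. Research assistants are not blinded (Intervention procedures).
2. Research assistants code the recordings, and a research assistant second-codes the reliability subset (Counselor fidelity measures).
3. Measuring bleeding and integrity supports two of the three reasons for crossing BHCs over arms (Discussion).

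Links 1 and 2 are stated. The Discussion does not name the instrument for bleeding. Linking it to the coded recordings is an inference, made because no other quantitative integrity measure is described.

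**Step 2. Size of the reliability subset.** 0.20 × 0.25 = 0.05, so 5% of all recordings are double-coded.

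**Step 3. What agreement can and cannot show.** Take one yes/no item, BI/RT+ content present on a BI/RT recording. All inputs here are assumed: true rate *t*, probability *s* that knowledge of arm makes a coder miss it, and random error *e* in either direction.

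If both coders miss on the same recordings, let *u* = *t*(1 − *s*). Then:

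- recorded rate *p* = *u*(1 − *e*) + (1 − *u*)*e*
- both coders positive *p11* = *u*(1 − *e*)² + (1 − *u*)*e*²
- observed agreement *po* = 1 − 2*p* + 2*p11*
- chance agreement *pe* = *p*² + (1 − *p*)²
- kappa = (*po* − *pe*)/(1 − *pe*)

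Example with *t* = 0.20, *s* = 0.5, *e* = 0.03, so *u* = 0.10:

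- *p* = 0.10 × 0.97 + 0.90 × 0.03 = 0.124
- *p11* = 0.10 × 0.9409 + 0.90 × 0.0009 = 0.0949
- *po* = 1 − 0.248 + 0.1898 = 0.9418
- *pe* = 0.0154 + 0.7674 = 0.7828
- kappa = 0.1590/0.2172 = 0.73

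| *t* | *s* | *e* | Recorded rate | Kappa, misses shared |
|---|---|---|---|---|
| 20% | 0 | 0 | 20% | 1.00 |
| 20% | 0.5 | 0 | 10% | 1.00 |
| 20% | 0 | 3% | 21.8% | 0.83 |
| 20% | 0.25 | 3% | 17.1% | 0.80 |
| 20% | 0.5 | 3% | 12.4% | 0.73 |
| 40% | 0 | 3% | 40.6% | 0.88 |
| 40% | 0.5 | 3% | 21.8% | 0.83 |

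If instead the two coders miss independently (*t* = 20%, *s* = 0.5, *e* = 0), the recorded rate is again 10%. Then *p11* = 0.20 × 0.5² = 0.05, *po* = 0.90, *pe* = 0.82 and kappa = 0.08/0.18 = 0.44. Agreement now drops, but a low kappa shows only that the coders differ, not which way they lean.

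**Step 4. The other direction.** If both coders wrongly flag a quarter of the clean recordings, with no random error, the recorded rate is 0.20 + 0.80 × 0.25 = 40%, again with kappa 1.00. High agreement is compatible with under-counting or over-counting.

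**The case against.** The blinding sentence follows the account of allocation and describes research assistants in general. The article does not say that coders were told the arm of a recording, that files carried arm labels, or that coders had enrolled the patients they coded. A fuller protocol or coding manual may describe masking. This is fair: it makes the point an exposure and not a demonstrated bias. It does not remove the point, because the article states that the group was unblinded, makes no exception for coding, and draws both coders from that group.

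The other objections narrow the consequence:

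- The SBIRT checklist already covers both arms' activities, so it can register cross-arm content. This stands. For the adherence-scale items the wording, "key BI/RT or BI/RT+ component items", leaves open whether every recording is scored on both sets. A complete list does not mask the person filling it in.
- A clinical supervisor reviews one to two randomly selected sessions per BHC each month and discusses protocol breaks. This helps limit contamination. It is not described as blinded, and its stated use is supervision.
- Much of the contrast is structural: one session against two to six, plus telephone monitoring in BI/RT+. Session counts do not depend on a coder's judgement.
- The article's main argument for crossing BHCs is that it equalises provider characteristics, which does not depend on coding.

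A reader might infer that bleeding will be under-counted, that agreement would be unaffected, and that the case for the crossed design therefore fails. The documents do not support this. They say nothing about direction. Agreement stays untouched only if both coders err on the same recordings without random error. The crossed design also rests on reasons that coders cannot affect.

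**Conclusion.** The point holds as a limited one. On the article's own words, the contamination and integrity measure comes from coders in an unblinded group, with no masking stated. It is open to expectation bias of unknown size and direction, and the planned double-coding cannot exclude an error that both coders share. The rates and kappas above rest on assumed inputs. They show what agreement can hide and estimate nothing about this trial.

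What is affected is the reading of contamination, any analysis relating integrity to outcome, and part of the justification for crossing BHCs. The primary outcomes, alpha and power are not affected. The conclusion assumes that the blinding sentence includes the coders and that the coded recordings are the measure of bleeding the Discussion has in mind. A statement that coders were masked would settle it.

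**What to change.** State whether coders were masked to arm. If they were not and coding is still to be done:

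1. Give recordings neutral file names without arm or session number.
2. Have existing research assistants code only patients they did not enrol.
3. Apply the adherence-scale items of both arms to every coded recording, as the checklist already does for activities.
4. Record each coder's guess of arm.

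If coding is finished, have existing research assistants re-code the double-coded 5% of recordings under the same masks and compare with the unmasked scores. First sessions should be the main comparison, because both arms have them and they give least away. Report unmasked coding as a limitation beside the paragraph on contamination.

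The cost is file renaming, reassignment of recordings among existing staff and some extra coding. Session content will sometimes reveal the arm, so masking reduces the risk without removing it. The recorded guesses show how often it failed.

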### Process evaluation and economic evaluation

In addition to the patient-level outcomes that we are assessing in the randomized controlled trial, we will analyze results from a process evaluation and will conduct an economic evaluation to further examine the impact of the BI/RT and BI/RT+ interventions.

#### Process evaluation

The data collected for the process evaluation focuses on quantitative and qualitative data from both providers and patients that will help in the interpretation of study results. The process data includes information about training of staff, the level of exposure of patients to the proposed intervention and the intensity of services received, and experiences of providers and patients and their satisfaction with the services being delivered. Data specifying the intensity of the enhanced brief intervention (BI/RT+) will be correlated with outcome measures of interest (e.g., reductions in substance use). Other data, such as the experiences of providers implementing the BI/RT and BI/RT+ protocols, will be useful for understanding the replicability in other primary care settings and the perceived burden of obtaining the changes observed relative to perceived and measured benefits. Data was primarily collected through semi-structured interviews with providers and patients, along with supporting quantitative data (e.g., length of implementation period, number of providers trained and frequency of trainings, number of BHC visits patients in the BI/RT+ condition received).

#### Economic evaluation

The economic evaluation has two primary components: (1) a societal-level cost-effectiveness evaluation and (2) a sustainability evaluation.

From a societal perspective, we hypothesize that BI/RT+ will have positive net social benefits relative to BI/RT alone. Net social benefits will be estimated as the difference in the additional benefits in dollar terms for BI/RT+ patients relative to BI/RT patients and additional costs for BI/RT+ patients relative to BI/RT. Benefits assessed will include economic benefits from crime avoided, enhanced job productivity, and downstream medical cost offsets. Costs assessed will include the costs of the intervention, such as fixed clinic costs, time and resources expended by clinic personnel delivering the intervention, and personal costs incurred by participants receiving the intervention (e.g., transportation expenses).

In addition to performing a societal-level economic evaluation, we will also develop a sustainability model for primary care clinics to help inform a decision regarding adoption of BI/RT or BI/RT+ in the future. Inputs for the model will consist of fixed costs for the intervention, such as training and space allocation, as well as variable costs that involve screening yield and productive use of the BHC. We will also model revenue sources and the ability to use codes which allow for billing of the screening. From this model, we will measure outcomes such as time to break-even costs of investing in SBIRT and return on investment in SBIRT for each of the sites included in this study.

### Data analysis

A total of 600 patients were randomized to the BI/RT or BI/RT+ conditions, and we stratified based on site, behavioral health consultant, and drug or alcohol severity (mild, moderate, or severe based on AUDIT or DAST-10 score). These stratification variables were chosen to account for possible differences in intervention delivery and treatment response. Specifically, we aimed to account for general site differences such as neighborhood/population served, typical amount of clinical contact received by patients, and range of services available. Similarly, we chose to stratify randomization by BHC in order to equalize non-specific provider variables across conditions. Because severity of substance use has consistently been demonstrated to moderate the impact of brief intervention on substance use [13], we equalized the proportion of mild, moderate, and severe substance use across conditions. Prior to performing all analyses, standard data screening/cleaning procedures will be applied. These procedures will (1) re-screen the data for data-entry errors, (2) check for outliers, (3) assess the extent and pattern of missing data, and (4) check that appropriate assumptions of normality are met and employ remedial measures such as power transformations whenever necessary. The randomization will be checked by comparing the groups on relevant background variables and on all baseline dependent measures. The comparisons will use analyses of variance for continuous variables and log-linear models for discrete or ordinal responses. Some covariates will be considered for inclusion in the main analyses to improve the precision of our hypothesis testing [56]. In addition, we have powered the study sufficiently to conduct subgroup analyses. Based on the literature, it is possible that patients who are using harder illicit drugs (cocaine, heroin, etc.) may respond differently to BI/RT and BI/RT+ than patients who are only using marijuana, or who use marijuana but primarily have a problem with alcohol. We will be adequately powered to break out these subgroups for secondary analysis. Below we specify each hypothesis and discuss the statistical procedures we will employ in analyzing the data.

